### Intervention

The interpretation of respiratory function tests and biomarkers will be performed by the principal investigator pulmonologist at each centre or by trained designated collaborating pulmonologists by following these models:

High-risk inflammatory asthma is defined by FeNO ≥25 ppb or BEC ≥300 cells/µL in participants ≥12 years (≥20 ppb or ≥300 cells/µL in children aged 6 to <12 years)^15 50^ : one or more elevated biomarkers will be interpreted as a high risk of asthma exacerbation. If spirometry is non-diagnostic, BPT will be prioritised (<2–4 weeks).Low risk inflammatory asthma is defined by FeNO <25 ppb and BEC <300 cells/µL (<20 ppb or <300 cells/µL in children aged 6–<12 years)^15 50^: this will be interpreted as a low risk of asthma exacerbation. If spirometry is non-diagnostic, BPT will be scheduled according to the standard waiting list.

Results of biomarkers will be integrated on the medical report indicating the probability (high/low) of asthma exacerbation and suggested management with either ICS taken as-needed (T2-low) or regularly (T2-High) ICS if clinically appropriate, which will be forwarded to the referring physician.

The patient test pathway based on their respiratory test and the results of the inflammometry assessment is summarised in figure 2.

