### Study visits

Study visits will coincide with medically recommended testing for suspected asthma (pre-/post-bronchodilator spirometry followed, if negative, with methacholine). Biobanking for DIVE and DIVE2 will only be conducted during methacholine visits. Electronic informed consent (and assent when applicable) will be obtained via REDCap.^33 34^ Additional data will be gathered on asthma exacerbation history and healthcare resource utilisation over the preceding year, including medications, by the use of reMed,^35^ a provincial research data repository of community pharmacy dispensed drugs that covers individuals under the public drug insurance plan.

During the single study visit, baseline bio-anthropometric and clinical data (age, sex, ethnicity, height and weight) will be collected. Participants will be interviewed regarding their medical history (smoking status, respiratory medication (with simultaneous carbon footprint calculation based on the number and type of inhalers delivered), recent (< 6 last weeks) respiratory infection and allergic history. Patients (and their legal guardian, if applicable) will complete standardised questionnaires on asthma control for the last 4 weeks (Asthma Control Questionnaire 5 (ACQ-5),^36^ Asthma Control Test (ACT)^37^ in adults and childhood Asthma Control Test (c-ACT) for children^38^ and of quality-adjusted life years (QALY) (EuroQol Five Dimensions Five Levels (EQ-5D-5L)^39 40^ for adults and EuroQol Five Dimensions Youth (EQ-5D-Y)^41^ for children).

Research respiratory therapists will first measure FeNO during a 10 s exhalation (6 s for children unable to cooperate, with a 10- s expiration)^31 42^ using NIOX VERO device (approved by Health Canada as a clinical tool). The latter was selected based on its established precision (coefficient of variation <10%), reproducibility and clinical validation.^43 44^ Then, blood samples will be collected for BEC either via capillary puncture (preferred for children), using the single-use Tasso+blood collection device (approved by Health Canada), or by venipuncture.^45^ For children, an anaesthetic cream, Ametop GEL 4% (tetracaine hydrochloride gel), will be offered to be applied to the puncture site 30 min before blood collection.^46^

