In patients consenting to participate in the DIVE or DIVE2 sub-study, supplementary biological samples will be collected during the methacholine visit, including the additional blood samples, nasosorption test for NELF and urine. The total volume of blood drawn from a child will adhere to Quebec’s standards for maximum blood volumes based on weight.^36^

Participants will then undergo spirometry or BPT with methacholine, depending on the visit, as per the diagnostic procedure.

Spirometry will be performed according to American Thoracic Society (ATS)/European Respiratory Society (ERS) standards, with reference values derived from the Global Lung Initiative 2022 race-neutral prediction equations.^47^ Patients will have been informed in advance of the need to withhold treatment as outlined in table 1.^48 49^

**Table 1 T1:** Recommended inhaler washout period prior to testing^48 49^

	Washout period	
	Spirometry	Bronchial provocation test
Short-acting β₂-agonists	> 4 hours	> 6 hours
Short-acting muscarinic antagonists	> 12 hours	> 12 hours
Long-acting β₂-agonists	> 36 hours	> 48 hours
Long-acting muscarinic antagonists	> 48 hours	> 1 week

Diagnostic criteria for asthma include:

Bronchodilator Reversibility Test: An increase in FEV₁ of ≥12% from baseline for all participants, with an additional criterion of ≥200 mL absolute improvement required for adults (≥18 years). Bronchodilator administration will be standardised using salbutamol 400 mcg delivered via spacer device.Methacholine BPT: Airway hyper-responsiveness, defined as a provocative dose causing a 20% decrease in FEV₁ (PD₂₀) of <400 mcg (equivalent to a provocative concentration (PC₂₀) of<16 mg/mL). While we acknowledge the more stringent European threshold (PD₂₀ ≤200 mcg, equivalent to PC₂₀ ≤8 mg/mL), we will adhere to our institutional protocols.^1^,^3^ The latter (European) diagnostic threshold will be evaluated through pre-planned sensitivity analyses.

At the end of the visit, all participants will complete a satisfaction questionnaire regarding the inflammatory biomarker testing and overall visit experience.

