### Data and sample management

Participant data will be collected prospectively in REDCap and stored on encrypted servers with restricted access hosted at the University of Sherbrooke.^33^ Follow-up will be conducted via REDCap emails with reminders after 15 days of no response.

BEC will be performed in each institution’s clinical laboratory (complete blood count with differential), after sampling in an EDTA tube. Blood samples will be processed within 4 hours of collection according to standardised protocols. For participants enrolled in the complementary DIVE or DIVE 2 studies, additional sample processing will include plasma separation, peripheral blood mononuclear cell separation and preservation of whole blood and DNA for future methylation analyses, following standardised biobanking protocols: inflammatory protein quantification will be performed on serum and NELF for IL-4, IL-5, IL-13, IL-33, thymus associated regulatory cytokine (TARC), thymic stromal lymphopoietin (TSLP), eotaxin-3, interferon gamma (IFNγ) and tumour necrosis factor (TNF) using multiplex electrochemiluminescent assays (MesoScale Discovery) and ELISA.

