#### Secondary Outcomes

Diagnostic accuracy of inflammometry assessed through receiver operating characteristic (ROC) curve analyses using FeNO levels, BEC and their combined values, with BPT as gold standard. Clinically relevant thresholds will be identified to optimise rule-in capacity for asthma diagnosis in primary care, targeting ≥90% of specificity and a positive likelihood ratio (LR+) ≥10 in children, adolescents and adults (as three distinct subgroups).Assessment of inflammatory status on asthma control, evaluated pre-diagnosis and post-diagnosis using the ACQ-5, ACT and EQ-5D-5L questionnaire scores. Additional measures include the number of exacerbations, prescribed and dispensed medications and the frequency of specialised asthma consultations collected from clinical records, drug claims and patient electronic reports at baseline and at 4-month, 8-month and 12-month follow-up.Assessment of health benefits in terms of QALY, budget impact and economic efficiency (evaluated using incremental cost-effectiveness ratio (ICER) and Incremental cost-utility ratio (ICUR)) of integrating inflammatory biomarkers into primary care asthma diagnosis.The evaluation of annualised carbon dioxide (CO2) emissions from inhalers dispensed to non-asthmatic individuals awaiting their diagnostic tests was done based on drug claims and Cascades Canada environmental data.^27^ Environmental sustainability assessment of biomarker-enabled pathways will be explored.Descriptive analysis of patient satisfaction regarding inflammometry and the overall experience of diagnostic procedures, with responses stratified by age (6–<12, 12–<18, ≥18) and diagnostic test (BDR or BPT) and final asthma diagnosis status.

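### The BPT reference for the accuracy analysis can be read with FeNO and BEC available; the numeric PD20 limit keeps the likely bias small, but the reading order should be fixed

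*Protocol article*

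**What the plan says.** All references are to the protocol article.

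- **Reference standard.** Secondary Outcomes plans ROC analyses of FeNO, BEC and their combination "with BPT as gold standard". It looks for rule-in cut-offs with specificity of at least 90% and LR+ of at least 10, separately in children, adolescents and adults.
- **Who reads.** Intervention states "The interpretation of respiratory function tests and biomarkers will be performed by the principal investigator pulmonologist at each centre". Other pulmonologists, trained and appointed for the task, may take this role instead. The biomarker results then go into the same medical report as the lung function result.
- **Order of tests.** Study visits states "Research respiratory therapists will first measure FeNO during a 10 s exhalation". Blood is drawn next, and after that "Participants will then undergo spirometry or BPT with methacholine, depending on the visit".
- **Booking.** For patients with at least one raised biomarker, Intervention states "If spirometry is non-diagnostic, BPT will be prioritised (<2–4 weeks"). The others stay on the standard list.
- **Positivity rule.** Study visits defines a positive BPT as a PD20 below 400 mcg and pre-plans a sensitivity analysis at the 200 mcg limit. Neither biomarker is part of the definition.

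**The concern.** In an accuracy study the reference result should be settled without sight of the index result. Here the text gives both readings to one role and one report, places FeNO ahead of the BPT, and lets biomarker status set the date of a BPT that follows a non-diagnostic bronchodilator test. Nothing in the article separates the two readings.

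FEV1 depends on effort. Whether a manoeuvre is acceptable, whether it is repeated, and how a fall close to 20% or a PD20 close to the limit is handled all need judgement. If that judgement leans towards positive in biomarker-high patients and towards negative in biomarker-low patients, index and reference agree more often than they should. Sensitivity, specificity and LR+ then all rise. LR+ at a rule-in cut-off is the exposed quantity, because its denominator rests on few false positives, and the analysis searches for cut-offs that reach 10.

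**Working it through.** The article gives no figure for this effect, so there is nothing to reproduce. The check has two parts.

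**1. What is known when the BPT is read**

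| Route to BPT | FeNO | BEC |
|---|---|---|
| BPT after an earlier bronchodilator visit | Known from that visit; reflected in the booking | Known from that visit; reflected in the booking |
| BPT on direct referral | Measured before the BPT; the text does not say who sees the value | Run in the hospital laboratory ("BEC will be performed in each institution’s clinical laboratory"); the text does not say whether the result is back in time |

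Prior knowledge is firm for the first route and only possible for the second.

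**2. How far LR+ could move**

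No input in this part comes from the article except the 2:1 ratio of asthma-positive to asthma-negative participants (Sample size, sub-studies), which supplies the 0.67 prevalence. The rest are assumptions. Let x be the share of readings swayed.

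- One-way: TP' = TP + x·FP and FP' = (1 − x)·FP.
- Two-way: also FN' = (1 − x)·FN and TN' = TN + x·FN.
- LR+ = [TP'/(TP' + FN')] ÷ [FP'/(FP' + TN')], with FN' = FN and TN' = TN in the one-way case.

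Worked example: 1000 tests, prevalence 0.40, sensitivity 0.35, specificity 0.95. Then TP = 140, FN = 260, FP = 30, TN = 570, and LR+ = 0.35/0.05 = 7.00. With x = 5%:

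- One-way: (141.5/401.5) ÷ (28.5/598.5) = 0.3524/0.0476 = 7.40.
- Two-way: (141.5/388.5) ÷ (28.5/611.5) = 0.3642/0.0466 = 7.81.

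Range over prevalence 0.40, 0.50 and 0.67, one-way and two-way, sensitivity 0.35:

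| x | True LR+ 3.50 (specificity 0.90) | True LR+ 7.00 (specificity 0.95) |
|---|---|---|
| 2% | 3.57–3.71 | 7.14–7.42 |
| 5% | 3.68–4.05 | 7.37–8.11 |
| 10% | 3.89–4.70 | 7.77–9.40 |
| 20% | 4.37–6.34 | 8.74–12.68 |

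In this grid LR+ passes 10 only from a start of 7.00 with 20% two-way influence.

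A cut-off that starts closer to the target needs fewer swayed readings. Assume 400 positive and 600 negative tests and sensitivity 0.30 (TP = 120), one-way influence only, with k = x·FP readings moved:

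- Specificity 0.97, FP = 18, LR+ 10.0. At x = 10%, k = 1.8: (121.8/401.8) ÷ (16.2/598.2) = 11.2. At x = 20%, k = 3.6: (123.6/403.6) ÷ (14.4/596.4) = 12.7.
- Specificity 0.9625, FP = 22.5, LR+ 8.0. At x = 10%, k = 2.25: (122.25/402.25) ÷ (20.25/597.75) = 9.0. At x = 20%, k = 4.5: (124.5/404.5) ÷ (18/595.5) = 10.2.

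With 270/730 or 590/410 positive/negative, the LR+ 10.0 case at x = 20% becomes 12.9 or 12.5.

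The targets apply by age group, so take a group of 200 tests with 80 positive, sensitivity 0.30 (TP = 24) and 4.5 expected false positives among 120 negatives (LR+ 8.0). One swayed reading gives (25/81) ÷ (3.5/119) = 10.5.

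If the label is computed from recorded values and acceptability is settled before the biomarkers are seen, the reader's contribution to x is 0 and LR+ stays at its true value.

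**The case against.** **A condensed article may leave masking to the full protocol.** This is fair as far as it goes, and the article commits to STARD reporting. But it is not merely silent: it states joint interpretation, FeNO first, and biomarker-driven booking. If the readings are in fact separated, that needs saying beside those statements.

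**The reference is already a number.** This largely stands. A PD20 limit leaves the reader little room, and the planned re-analysis at 200 mcg presupposes recorded values. However, the article does not say that the ROC label is computed from those values rather than taken from the pulmonologist's report. Changing the limit reuses the same tests and so does not remove influence on acceptability or repeats.

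**The lock does not reach the therapist.** This stands. Knowledge of FeNO could affect coaching while the test is run, and a reading order cannot prevent that. Nor can the lock erase what a reader remembers from reporting an earlier bronchodilator visit.

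**Stronger readings that the text does not support.** A reader might infer that:

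- one person always reads both tests for each patient; Intervention names a role, with alternates;
- both biomarkers are always known before the BPT; this is firm only after an earlier bronchodilator visit;
- the bronchodilator test is also the accuracy reference; Secondary Outcomes names BPT alone;
- LR+ will be inflated by the amounts shown above; those rest on assumed rates, and a 20% rate is hard to credit against a numeric limit.

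**Conclusion.** The point holds in a limited form. As written, the BPT that serves as the reference can be read with FeNO and BEC available, most clearly when it follows an earlier bronchodilator visit. The numeric PD20 rule confines possible bias to acceptability, repeat manoeuvres and near-limit calls. The direction would be upward for specificity and LR+. The size cannot be derived from the article and is probably small: in the grid with sensitivity 0.35, influence of 2% to 5% moves an LR+ of 7.00 to between 7.14 and 8.11. The larger shifts show that a cut-off near the LR+ target is sensitive to a few readings, above all within one age group. They are not estimates of expected bias. Only the secondary accuracy outcome is affected; diagnostic delay, the primary outcome, is not. The change is worth making because it is cheap and because selectively accepted tests cannot be fully corrected afterwards.

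**What to change.** In Intervention, Secondary Outcomes and the diagnostic-performance paragraph of Statistical methods:

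1. State that, for the accuracy analyses, the BPT label is derived by program from the recorded FEV1 and PD20 values and the limit already given in Study visits.
2. Have the reader enter and lock test acceptability and the BPT result (positive, negative or uninterpretable) in REDCap before opening the FeNO and BEC fields. Add the biomarker interpretation and issue the combined report to the referrer only after the lock.
3. Report as limitations that the therapist running the test is not masked, and that a reader may already know the biomarker status from an earlier visit or from the booking.

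The cost is one locked form and a report completed in two steps. No extra reader, visit or test is needed, and the triage rule and the content of the referrer's report do not change.

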**Methods and analysis:**

Three academic centres in Québec will measure inflammatory biomarkers alongside BDR and/or BPT interpretation for patients with suspected asthma referred by primary care providers (PROPULSION SANTÉ, NCT06981169). Consenting patients aged ≥6 years will undergo FeNO, BEC and BDR testing. If BDR is non-diagnostic, subsequent BPT will be prioritised for patients with ≥1 elevated biomarker (BEC ≥300 /µL, (FeNO ≥25 ppb if ≥12 years or FeNO ≥20 ppb if <12 years)); others will follow usual timelines. Reports to the referring healthcare providers will include standard interpretation of BDR/BPT and biomarker results to state exacerbation risk and suggested corticosteroid dosage. Asthma control and quality of life will be assessed at baseline and remotely at 4, 8 and 12 months. The primary outcome will be the delay from the reception of test request for the diagnosis of asthma patients with versus without elevated biomarker(s). Secondary outcomes include biomarkers’ diagnostic performance, asthma control, quality of life, health benefits, cost-effectiveness, environmental impact and patient satisfaction. We aim to recruit 1500 patients to PROPULSION SANTÉ, with optional biobanking for translational sub-studies for 123 adults (DIVE, NCT05992519) and 123 children (DIVE2, NCT07011394).

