**Figure 2 F2:**
[figure not shown]
Flow Diagram. Patients with suspected asthma are referred by primary care for pulmonary function testing (BDR or BPT). Those who consent to participate in the study will undergo BEC and FeNO testing. Patients with normal spirometry results and at least one elevated inflammatory marker will have their methacholine challenge test prioritised. If no inflammatory markers are elevated, the BPT will be scheduled within standard timelines. Patients undergoing a BPT—either directly on referral or after an initial BDR—will be invited to participate in the translational research studies, DIVE for adults or DIVE2 for children. Patients with a confirmed diagnosis of asthma (based on spirometry or BPT) will also be stratified according to their inflammometry results, which will be included in the report sent to the referring physician. BEC, blood eosinophil count; BDR, bronchodilator reversibility; BPT, bronchial provocation testing; FeNO, fraction exhaled of nitric oxide.

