For the primary outcome of waiting time differences, the baseline diagnostic delay, prior to the project implementation, will be established based on the time elapsed between the initial request for an asthma diagnostic test made by primary care and the performance of that test. During the intervention, diagnostic delays will be monitored prospectively, both overall and stratified by inflammatory status. We will apply linear mixed-effects models with restricted maximum likelihood estimation. These models will incorporate (high-risk vs low-risk), study period at time of inclusion, and the number of awaiting tests as fixed effects. Random effects will account for within-centre clustering and repeated measurements. In addition, Kaplan-Meier survival curves will be constructed to visualise the probability of remaining undiagnosed over time for both high-risk and low-risk inflammatory phenotypes. These curves will allow for a graphical representation of differences in diagnostic efficiency between groups. Cox proportional hazards regression will be used to identify significant predictors of waiting time with HRs and 95% CIs reported.

Diagnostic performance in the secondary outcome will be evaluated through ROC analysis, calculating the area under the curve (AUC) with 95% CIs for each individual marker and for their combined use. Sensitivity, specificity, positive and negative predictive values and likelihood ratios will be calculated with their respective 95% CIs.

Health utility values will be derived from EQ-5D questionnaires^39 52 53^ completed at baseline and follow-up visits. Quality-adjusted life years will be calculated using the AUC method, connecting utility values across measurement time points. This approach integrates health-related quality of life over the 12-month follow-up period. To assess the financial implications of implementing FeNO testing within the provincial healthcare framework, we will develop a budget impact model for the MSSS. Environmental and satisfaction-related outcomes will be analysed using descriptive statistics. CO₂ emissions from inhalers dispensed to non-asthmatic individuals will be estimated based on Cascades Canada data,^27^ and patient satisfaction with inflammometry will be assessed using structured questionnaires.

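### The low-risk definition for children aged 6 to <12 years is joined by *or* instead of *and*, so a child with exactly one elevated biomarker is both high and low risk

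*Protocol article*

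**What the plan says.** The Intervention section of the protocol article sets out the two classes that the interpreting pulmonologists are to use.

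- **High risk, 6 to <12 years:** "≥20 ppb or ≥300 cells/µL in children aged 6 to <12 years". The article then adds, without an age limit, that "one or more elevated biomarkers will be interpreted as a high risk of asthma exacerbation".
- **Low risk, 12 years and over:** "Low risk inflammatory asthma is defined by FeNO <25 ppb and BEC <300 cells/µL".
- **Low risk, 6 to <12 years:** given in brackets straight after the older group's rule, as "<20 ppb or <300 cells/µL in children aged 6–<12 years".

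The same rule appears in two other places. The Abstract (Methods and analysis) says that "subsequent BPT will be prioritised for patients with ≥1 elevated biomarker", and everyone else follows usual timelines. The Figure 2 caption says: "If no inflammatory markers are elevated, the BPT will be scheduled within standard timelines".

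The class is used in three ways. When spirometry is non-diagnostic it decides between a prioritised provocation test (<2–4 weeks) and the standard waiting list. It determines the report to the referrer, which gives a high or low exacerbation probability and "suggested management with either ICS taken as-needed (T2-low) or regularly (T2-High) ICS if clinically appropriate". It also enters the primary analysis; in Statistical methods, "These models will incorporate (high-risk vs low-risk), study period at time of inclusion".

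**The concern.** Two classes meant to divide the children between them should be complements. The complement of *A or B* is *not A and not B*. The low-risk rule for participants aged 12 and over follows this, but the bracketed rule for younger children keeps *or*. A child with one raised and one normal marker therefore meets both definitions.

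For such a child the text points at once to a prioritised test and to the ordinary queue, where the Introduction reports waits of more than a year. It also points to high and low exacerbation risk, and to regular and as-needed inhaled corticosteroid. Because the class drives the scheduling that the primary outcome measures, a child queued under the wrong reading would also blur the high-risk versus low-risk contrast.

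**Working it through.** The article gives no figure to reproduce here; the check is one of logic.

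**Inputs** (Intervention section, ages 6 to <12 years): FeNO cut-off 20 ppb and BEC cut-off 300 cells/µL. The Abstract gives the same two cut-offs.

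**Rules:**

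- High, as printed: FeNO ≥20 *or* BEC ≥300
- Low, as printed: FeNO <20 *or* BEC <300
- Low, corrected: FeNO <20 *and* BEC <300

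**All four combinations:**

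| FeNO ≥20 | BEC ≥300 | High (printed) | Low (printed, *or*) | Low (corrected, *and*) | In both, printed | In both, corrected |
|---|---|---|---|---|---|---|
| no | no | no | yes | yes | no | no |
| no | yes | yes | yes | no | **yes** | no |
| yes | no | yes | yes | no | **yes** | no |
| yes | yes | yes | no | no | no | no |

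**Counts:**

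- As printed: high covers 3 of 4 combinations and low covers 3 of 4. Together they cover all 4, so the overlap is 3 + 3 − 4 = 2, namely the two rows with exactly one elevated marker.
- Corrected: high covers 3, low covers 1, and 3 + 1 − 4 = 0 overlap. Every combination falls in exactly one class, as it already does at 12 years and over.

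**Worked example:** FeNO 30 ppb, BEC 100 cells/µL. High risk holds because 30 ≥ 20. Low risk as printed also holds because 100 < 300. Corrected low risk fails because 30 is not below 20.

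**Agreement with the other statements:** for one elevated marker, the unrestricted sentence in the Intervention section, the Abstract and the Figure 2 caption all give high risk. Only the bracketed low-risk rule for young children says otherwise.

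The count of 2 in 4 refers to logical combinations, not to patients. The article gives neither the number of participants aged 6 to <12 years nor how often each marker is raised in them.

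**The case against.** The strongest reply is that the article resolves the ambiguity itself. The sentence on one or more elevated markers carries no age restriction and comes just before the low-risk rule; the Abstract and the Figure 2 caption agree with it, and nothing supports the opposite rule. The bracket can be read as merely supplying the children's cut-offs for the rule before it, with the connective copied from the high-risk bracket. Interpretation is in the hands of site pulmonologists or trained designated colleagues, who would have to overlook the preceding sentence to go wrong. The article also condenses a fuller protocol that is not shown, and the document used at the centres may be worded correctly.

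Most of this stands. The intended rule is clear, no misclassification or difference between sites is shown, and the analysis class can be rebuilt from the numeric values. That keeps the point minor but does not remove it. The conflict lies in the sentence that defines the class, and the article tells interpreters to follow these definitions. A test date or report already issued on the wrong reading could not be recovered by reclassifying the data later.

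**Conclusion.** The concern holds, as a minor error with high confidence. As printed, the low-risk rule at 6 to <12 years overlaps the high-risk rule in 2 of the 4 marker combinations, exactly those with one elevated marker, and contradicts the article's other statements of the rule. It is very probably a drafting slip. The conclusion rests only on the printed definitions and needs no outside assumption. No sample size, power or alpha figure is affected, and participants aged 12 and over are not touched. The share of children concerned is unknown.

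**What to change.** In the Intervention section, change the low-risk rule for ages 6 to <12 years to FeNO <20 ppb *and* BEC <300 cells/µL. Confirm with the three centres that any elevated marker is being treated as high risk when tests are scheduled and reports written. For the analysis, derive the high/low class from the recorded FeNO and BEC values by that rule.

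The cost is one word in the text and one confirmation with the centres.
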